## Abstract

**Introduction:**

Recognising prematurity is critical in order to attend to immediate needs in childbirth settings, guiding the extent of medical care provided for newborns. A new medical device has been developed to carry out the preemie-test, an innovative approach to estimate gestational age (GA), based on the photobiological properties of the newborn’s skin. First, this study will validate the preemie-test for GA estimation at birth and its accuracy to detect prematurity. Second, the study intends to associate the infant’s skin reflectance with lung maturity, as well as evaluate safety, precision and usability of a new medical device to offer a suitable product for health professionals during childbirth and in neonatal care settings.

**Methods and analysis:**

Research protocol for diagnosis, single­group, single­blinding and single­arm multicenter clinical trial with a reference standard. Alive newborns, with 24 weeks or more of pregnancy age, will be enrolled during the first 24 hours of life. Sample size is 787 subjects. The primary outcome is the difference between the GA calculated by the photobiological neonatal skin assessment methodology and the GA calculated by the comparator antenatal ultrasound or reliable last menstrual period (LMP). Immediate complications caused by pulmonary immaturity during the first 72 hours of life will be associated with skin reflectance in a nested case–control study.

**Ethics and dissemination:**

Each local independent ethics review board approved the trial protocol. The authors intend to share the minimal anonymised dataset necessary to replicate study findings.

**Trial registration number:**

RBR-3f5bm5.

Strengths and limitations of this study:Prospective multicenter evaluation of a new medical device with training, and certification of collaborative centres.The gold standard comparator for pregnancy dating does not exist; instead a reference standard will be used with blinded primary outcome.The agreement endpoint between methods for gestational age determination precludes randomisation of the intervention.

## Introduction

In childbirth settings, health professionals continuously need to make timely decisions to provide proper neonatal care. The day of birth is the riskiest for newborns and mothers almost everywhere.^1^ Perinatal causes related to prematurity and complications during childbirth, which are generally preventable through qualified healthcare, are the primary causes of death among newborns.^1 2^ Most of these deaths take place in countries with low resources and a scarcity of health facilities.^3^ The opportune recognition of prematurity is critical in order to judge the viability of the newborn and to attend to his immediate needs, guiding the complexity of the medical care provided for the newborn. Without reliable information on the age of the unborn phase, actions to preserve the potential for survival of the newborn can be neglected.^4^ Indeed, the attempted management of the risk of mortality and severe complications are sensitive issues to the gestational age (GA), which involves temperature maintenance, ventilatory support, transport to a neonatal intensive care unit (NICU), and the early treatment of respiratory distress syndrome (RDS), the most severe complication of premature birth.^5^ In addition to the GA information or birth weight, the prediction of neonatal respiratory morbidity may be critical in planning immediate medical care,^6^ since the respiratory system is among the last of the fetal organ systems to mature, which is associated with enhanced morbidity and mortality.^6^

Current methods of dating pregnancy remain a worldwide challenge. Early obstetric ultrasound currently offers the best due date.^7^ However, access to this type of exam is limited because of high equipment costs, poor training and skills of health professionals, or late prenatal care.^8^ Despite a 10-days or more margin of error during the second and third trimester of gestation, ultrasound is still a reasonable methodology for GA determination, when the best opportunity was lost.^7^ The calculation, based on the historical information of the last menstrual period (LMP), is impacted by the uncertainty of both the fertility days and date of conception,^9^ due to the bias of memory, the use of hormonal contraception and breastfeeding.^10^ After birth, neurological scores, such as the New Ballard,^11^ show a tendency to overestimate GA in preterm infants and underestimate GA in growth-restricted infants.^12^ Efforts to enhance the reliability of pregnancy dating, through more accurate and accessible technologies, seek to improve pregnancy outcomes and neonatal survival.^13^

A new medical device has been developed to carry out the preemie-test, an innovative approach used to estimate GA, based on the photobiological properties of the newborn’s skin. This reflective test is non-invasive, and the device automatically processes the light, scattered by the constituents of the skin layers, when a small optoelectronic light emitter/receiver sensor touches the newborn’s skin.^14^ The device under test is easy to use and every effort is being made to ensure that it has excellent accuracy, be it safe and low cost. The feasibility study provided a mathematical model to predict GA based on the skin reflectance adjusted to clinical variables (R^2^=0.828, p<0.001).^15^ However, before the adoption or use of an innovation, an effectiveness trial of intervention is a critical step in the research chain regarding its the social utility when completing the translation from the proof of concept to clinical science.^15^ The rationale for the main hypothesis in this study is that the skin maturity of a newborn, obtained by the analysis of its optical properties, is useful in pregnancy dating for clinical use and respiratory prognosis, especially in a scenario with no reliable GA based on current methods. This study aims to validate the photobiological model of the skin, called the ‘preemie-test’, in order to estimate GA at birth and determine its accuracy in detecting prematurity. Second, it also seeks to associate the infant’s skin reflectance with lung maturity. Moreover, this study intends to evaluate the safety, precision and the usability of a new medical device to offer a suitable product to support health professionals during childbirth and in neonatal care settings.

## Methods

### Study design

This study will use a protocol for diagnosis, single­group, single­blinding and single­arm multicenter clinical trial with a reference standard. This new photobiological approach to the skin, gathered in a medical device, is currently in the pivotal phase of innovation development from the prototype to regulatory approval.^16^ This step aims to provide the translation^15^ of the scientific model for GA detection based on skin maturity. This Protocol version is 2, 15 January 2019. Faculty of Medicine, Universidade Federal de Minas Gerais is the Coordinator Centre.

### Study settings, ethics and dissemination

Selected Brazilian referral centres for high-risk pregnancy and neonatal care will participate in the study, according to this protocol: Hospital das Clínicas, Universidade Federal de Minas Gerais, as the Centre for Coordination; Hospital Sofia Feldman, Minas Gerais State; Hospital da Universidade Luterana do Brasil, Rio Grande do Sul State; Hospital Materno-infantil de Brasília, Distrito Federal; and Hospital Universitário da Universidade Federal do Maranhão, Maranhão State. Each local independent ethics review board approved the trial protocol, and the Brazilian National Research Council approved all study activities and protocol prior to the commencement of study activities, in accordance with the Declaration of Helsinki (2008), good clinical practice as set forth by the International Organization for Standardization 14155:2011, and the Brazilian regulatory health agency’s recommendations.^17^ This study was logged under both protocol number CAAE 81347817.6.1001.5149 and the International Clinical Trials Registry Platform under number RBR-3f5bm5. Parents will sign an informed consent form on behalf of the newborn before participating in the clinical trial (online supplementary file).

10.1136/bmjopen-2018-027442.supp1Supplementary file 1

### Patient and public involvement

Patients and the public were not involved in the design of this study. The results will be disseminated to study parents of participants through scientific publications, non-scientific publications and on the website of the project: http://skinage.medicina.ufmg.br.

### Eligibility criteria and participant’s timeline

A prospective sequential and concurrent enrollment process will select newborns in referral hospitals centres for neonatal care. Infants are eligible with the following inclusion criteria: (1) alive newborn; (2) enrollment during first 24 hours of life; (3) be 24 weeks or more of GA, at birth; (4) fetus underwent an obstetric ultrasound assessment before 14 weeks of pregnancy and (5) fetus also had obstetric ultrasound assessment between 14 and 22 gestational weeks. Exclusion criteria are: (1) malformation with structural skin alterations and (2) skin modifiers: anhydramnios, hydrops, congenital skin diseases or chorioamnionitis. Randomisation was not appropriate to assess the agreement between different methods to assess pregnancy dating.

In a nested case–control study, we will select newborns within the first 72 hours of life, discharge or death, whichever occurs first, with the following inclusion criteria: (1) RDS or (2) tachypnoea of the newborn (TTN) diagnosis. Ranges of GA will randomly pair controls. Exclusion criteria include: (1) the existence of extra pulmonary conditions with tachypnoea not due to prematurity and (2) diagnosis of Clinical or Laboratory-Confirmed Bloodstream Infection.

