### Secondary outcome measures

In a simulated scenario, in which the Reference-GA (R) is unknown, two groups will be randomly assigned from the complete database in order to compare differences among the Reference-GA (R), the GA obtained through the preemie-test (T) and the GA calculated by the comparators. Figure 1 presents such subgroups and measures for comparison.To monitor the device’s safety when in regular use by participants over a 72-hours period. Adverse events will be monitored, according to ISO 14155:2011 standards. This means any unexpected medical events, unintended disease or injury or unfortunate clinical signs in subjects, users or other people, whether related to the investigational medical device or not.To establish the *ease of use* of the preemie-test measurement as a potential method for preterm newborn diagnosis.

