### Sampling and sample size

The sample size calculation is estimated based on the primary endpoint. To test the hypothesis of equivalence between the preemie-test GA and the comparators GA, a sample of 787 subjects is necessary to detect an effect size of 10%. Using the G-Power 3.1 software,^20^ we assumed an alpha error of 0.05 and a power of test of 0.80 to support a paired t-test.

Sampling intends to arrange three groups of GA enrolment to preserve enough premature newborns with 3:2:1 proportion, similar to Wilson *et al*^21^: 392 term newborns, 263 premature newborns from 32 to 36 weeks and 6 days of GA and 132 extremely premature newborns from 24 to 31 weeks and 6 days of GA.

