### Data analysis

Demographics and baseline characteristics of the study group, as well the intervention measurements, will be summarised by the frequencies and the mean and standard deviation (SD), whereas the median and interquartile range (IQR) will be preferred for non-normally distributed continuous variables.

To model the GA prediction, computational randomisation will select two subsamples in the database. One of them to train the prediction model of GA based on skin reflectance and clinical variables, such as sex, time in an incubator, phototherapy, birth weight, among others. Another part will be for the analytical validation of the predictive model. Improvements in the existing prediction models for GA (preemie-test), will be conducted with conventional statistical and data mining analyses.

Regarding the primary endpoint, the agreement among three methods for GA will be calculated using the Intraclass coefficient correlation and Bland & Altman plots,^23^ and paired t-testing. The accuracy of the preemie-test in identifying the premature newborn, within a 1-week margin of error, will be the target of the accuracy analysis.

The relationship between the measurement of the newborn’s skin reflectance and complications due to pulmonary distress associated with immaturity will be evaluated by means of association tests and risk. The significance level for hypothesis tests will be 5%, together with 95% CIs.

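### Twins are eligible, but the sample size and paired t-test treat all infants as independent, and the training/validation split does not say that siblings stay together

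*Protocol article*

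**What the plan says.** All references are to the Methods of the protocol article.

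- **Eligibility criteria and participant's timeline.** The unit of enrolment is the newborn: "Infants are eligible with the following inclusion criteria: (1) alive newborn". The exclusions concern the skin only: "Exclusion criteria are: (1) malformation with structural skin alterations and (2) skin modifiers: anhydramnios, hydrops, congenital skin diseases or chorioamnionitis". Multiple pregnancy is mentioned neither here nor elsewhere in the article.
- **Study settings, ethics and dissemination.** "Selected Brazilian referral centres for high-risk pregnancy and neonatal care will participate in the study".
- **Sampling and sample size.** The article states that "a sample of 787 subjects is necessary to detect an effect size of 10" per cent, and "we assumed an alpha error of 0.05 and a power of test of 0.80 to support a paired t-test". The quotas are "392 term newborns, 263 premature newborns from 32 to 36 weeks and 6 days of GA and 132 extremely premature newborns".
- **Gestational age methods of calculation and comparators.** The reference (R) comes from the early scan, the first comparator (C1) from a later scan before 22 weeks, and the second comparator (C2), where available, from the mother's LMP.
- **Data analysis.** Agreement is assessed by intraclass correlation, Bland–Altman plots and paired t-tests, with no term for the pregnancy. For model building, "computational randomisation will select two subsamples in the database", one for training and one for validation. Neither the unit of that randomisation nor the split fraction is given.
- **Secondary outcome measures.** A further random division is planned, also without a stated unit: "two groups will be randomly assigned from the complete database".

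**The concern.** A paired t-test removes the dependence between two measurements on one infant. It does not remove the dependence between two infants from one pregnancy. C2 is the same date for both siblings, and the scans behind R and C1 will usually have been done at the same visits. Part of the dating error is therefore shared, and the test-minus-comparator differences (T−C) of siblings are likely to be positively correlated. If so, counting each sibling as a full independent observation gives standard errors that are too small and fewer effective observations than 787.

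The split raises a separate question. If it is made infant by infant, a validation infant may have a sibling in the training set with nearly the same gestational-age label. The validation would then not be fully independent of the training. The article describes the study as the pivotal phase before regulatory approval, where both interval width and an honest validation error matter.

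**Working it through.** **1. Reproduce the plan's figure.** Inputs from Sampling and sample size: standardised paired effect 0.10 (reading the 10 per cent this way), alpha 0.05, power 0.80, paired t-test. With the noncentral t distribution and a two-sided test, power is 0.7996 at n = 786 and 0.8001 at n = 787, so 787 is reproduced exactly. The normal approximation, ((1.960 + 0.842)/0.10)², gives 785. A one-sided test gives 620 and does not fit. The 787 is therefore the size for 787 independent differences, with no design effect.

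**2. Why twins are to be expected.** The quotas sum to 392 + 263 + 132 = 787, of which 263 + 132 = 395 (50.2%) are preterm. Together with the high-risk referral setting, this favours multiples. The article does not say by how much.

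**3. Design effect.** Let f be the share of enrolled infants whose co-twin is also enrolled, and rho the within-pair correlation of T−C. Each paired infant adds one covariance term, so Var(mean) = (σ²/n)(1 + f·rho) and DE = 1 + f·rho. The true SE is √DE times the naive SE, and the effective n is 787/DE. Neither f nor rho is in the documents. The range below is an assumption, applied to the full 787.

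| f | rho | DE | True SE / naive SE | Effective n | Power |
|---|---|---|---|---|---|
| 0.05 | 0.3 | 1.015 | 1.007 | 775 | 0.794 |
| 0.05 | 0.5 | 1.025 | 1.012 | 768 | 0.790 |
| 0.10 | 0.5 | 1.050 | 1.025 | 750 | 0.781 |
| 0.20 | 0.5 | 1.100 | 1.049 | 715 | 0.762 |
| 0.25 | 0.8 | 1.200 | 1.095 | 656 | 0.725 |

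To restore the planned power, N would be 787 × DE: 799 in the first row and 945 in the last.

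**4. Limits of agreement.** These are the mean ± 1.96 SD. Under this clustering the expected sample variance is σ²(n − DE)/(n − 1). In the last row that is (787 − 1.20)/786 = 0.99975 of σ², so the SD is low by about 0.013%. The limits do not move in any practical sense. Their confidence intervals do, because these rest on the effective number of observations.

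**5. The split.** If it were made by infant with training share p, a twin pair would be separated with probability 2p(1 − p), and a share f·p of validation infants would have a sibling in training. At p = 0.5 and f = 0.05–0.25 that share is 2.5–12.5%. This counts the exposed infants; it does not measure any change in prediction error.

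**The case against.** Five points can be made on the other side.

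- **A condensed article may leave this to the SAP.** This stands for the unit of the split and for details of variance estimation, taken as omissions. It does not remove the point, because the article itself fixes per-newborn eligibility, a sample size with no design effect and the paired t-test. Together these assume independence that the eligibility rule does not secure.
- **Sibling leakage is not in the text.** This stands. A reader might infer that the plan randomises infants and so puts siblings on both sides. The article names no unit, so this is a risk only. Its effect may also be small: with a 50:50 split, about 390 training infants would already cover most gestational ages.
- **The limits of agreement are not narrowed by clustering.** This stands. It is tempting to say they are too narrow, but step 4 shows that only their intervals are affected.
- **Not every date belongs to the pregnancy.** This stands in part. R rests on an embryo measurement, and eligibility refers to the scans of the fetus, so R and C1 could differ between siblings. Only C2 is necessarily common, and only where it is available. A positive correlation is likely, but its size is unknown.
- **A co-twin can be a legitimate control.** This stands. The nested study pairs controls by range of gestational age, and nothing in the article makes a sibling control an error.

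**Conclusion.** The point holds in a limited form. Multiples are eligible, and both the sample size and the named primary test treat every infant as independent. Confidence intervals for the mean T−C difference, around the limits of agreement and for the detection proportion are therefore likely to be somewhat too narrow. For the mean T−C difference, with 5–25% of infants in enrolled pairs and a correlation of 0.3–0.8, the design effect is about 1.02–1.20, the true standard error is about 1–10% above the naive one, and power is about 0.79–0.72. Both ranges are assumptions. With few complete pairs, the effect is near the bottom of the range.

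The direction is clear if the correlation is positive, and the size is modest. A reader might conclude that the primary result would be invalid or the validation contaminated. The documents support neither: the inflation is small over the range shown, and the split unit is simply not stated. The point is worth settling because the remedy costs little and the split rule must be fixed before the model is trained; a leak found later could be undone only by refitting.

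**What to change.** - In Data analysis, state that the training/validation randomisation is by pregnancy, so that siblings always fall in the same subsample. Apply the same rule to the random groups in Secondary outcome measures.
- Compute standard errors and confidence intervals for the mean T−C difference, the limits of agreement and the detection proportion clustered by pregnancy, using cluster-robust variances or a bootstrap that resamples pregnancies.
- Add a sensitivity analysis that keeps one randomly chosen infant per pregnancy.
- Report the number of infants from multiple pregnancies and of complete enrolled sets, so that the real design effect can be seen.

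The cost is a pregnancy identifier in the database, a small amount of analysis code and slightly wider intervals. No change to eligibility, recruitment or procedures is needed.

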### The secondary outcome measures in the case–control nested study

Immediate complications, occurring during the first 72 hours of life due to pulmonary immaturity, are the secondary target. The outcome measures are as follows:To describe the relationship of the measurement of the newborn’s skin reflectance with RDS and with diagnoses based on clinical and radiological findings and respiratory outcomes.^6 19^To describe the relationship of the measurement of the newborn’s skin reflectance with the TTN and with diagnoses based on clinical findings and respiratory outcomes.^6^To describe the relationship of the measurement of the newborn’s skin reflectance with ventilatory support due to pulmonary immaturity.To describe the relationship of the measurement of the newborn’s skin reflectance with NICU admission due to RDS or TTN.

Time schedule of enrolment, intervention and outcome measurements are presented in a schematic diagram (see figure 2). The assessment occurs during the first 24 hours of life, but participants will be followed-up for 72 hours or until discharge or death, whichever occurs first, for the monitoring of neonatal outcomes and adverse events.

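### The GA-paired nested study tests reflectance at a given GA; a full-cohort analysis is needed for respiratory prognosis where GA is unknown

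*Protocol article*

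**What the plan says.** The Introduction gives the main hypothesis: skin maturity "is useful in pregnancy dating for clinical use and respiratory prognosis, especially in a scenario with no reliable GA based on current methods". The secondary aim that follows is looser; the study "seeks to associate the infant’s skin reflectance with lung maturity". Earlier, the Introduction presents respiratory prediction as something beyond GA: "In addition to the GA information or birth weight, the prediction of neonatal respiratory morbidity may be critical in planning immediate medical care".

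Under Eligibility criteria and participant's timeline, the nested case–control study takes newborns with RDS or TTN as cases. On controls it says only: "Ranges of GA will randomly pair controls". The width of the ranges is not given.

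The section on secondary outcomes of the nested study lists four descriptive relationships of reflectance: with RDS, TTN, ventilatory support and NICU admission. The first reads "To describe the relationship of the measurement of the newborn’s skin reflectance with RDS". The Abstract also places the pulmonary complications in the nested study. Under Data analysis, this relationship "will be evaluated by means of association tests and risk".

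Reflectance is stored for every newborn (Intervention section). All participants are followed for 72 hours, or until discharge or death (nested-study outcomes section).

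**The concern.** The device is developed because reflectance tracks GA. A birth attendant with no reliable GA who uses reflectance to judge respiratory risk is using mostly that GA-carried information. The relevant contrast for that user is affected against unaffected infants across all GAs.

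The contrast described for the lung outcomes holds GA roughly fixed. What is left is any effect of reflectance that is independent of GA, plus whatever GA differences remain inside a range. So the paired study answers whether reflectance adds something once GA is known. A small or null paired result is compatible with good prognostic performance where GA is unknown, and the article does not say how such a result should be read.

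The dating aim is handled differently. The Secondary outcome measures section builds a simulated scenario in which the reference GA is unknown. The lung aim has no counterpart to this.

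**Working it through.** **The plan's own figures.** The nested study has no stated sample size, power or effect size, so there is nothing to reproduce for it. The trial total of 787 does reproduce: a two-sided paired t-test at alpha 0.05 with standardised effect 0.10 has power 0.8001 at n = 787. The quotas add up: 392 + 263 + 132 = 787. Neither figure bears on this point; the quotas are used below only for the GA mix.

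**Inputs from the article**
- GA mix 392 : 263 : 132 (term; 32 to 36 weeks 6 days; 24 to 31 weeks 6 days), from Sampling and sample size.
- R² = 0.828 for the feasibility model, from the Introduction. That model was adjusted to clinical variables, so 0.828 is probably an upper value for reflectance alone. R² of 0.5 and 0.7 were run as well.

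**Assumptions (not in the article)**
- GA uniform within each group, with term taken up to 42 weeks.
- Reflectance score x = √R² · z(GA) + √(1 − R²) · e, where z(GA) is standardised GA and e is standard normal noise.
- Risk of RDS/TTN: logit P = −s(GA − m) − g·e, with s = 0.3, 0.5 or 0.7 per week and m = 32 or 33 weeks. The GA-independent effect is g = 0, 0.3 or 0.6 log-odds per residual SD. About 26 to 29% of the cohort become cases.
- One control per case, drawn at random within 1-week ranges, 2-week ranges or the three enrolment groups.

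**Measure.** Share of signal lost = (AUC unmatched − AUC paired) / (AUC unmatched − 0.5), from 400,000 simulated newborns per scenario.

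**Example, R² = 0.828, s = 0.5, m = 33**

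| | Unmatched | 1-week | 2-week | Three groups |
|---|---|---|---|---|
| AUC, g = 0 | 0.875 | 0.504 | 0.512 | 0.598 |
| Share lost | – | 99% | 97% | 74% |
| AUC, g = 0.6 | 0.902 | 0.574 | 0.581 | 0.666 |
| Share lost | – | 82% | 80% | 59% |

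For the three groups: (0.875 − 0.598)/(0.875 − 0.5) = 0.277/0.375 = 0.74, and (0.902 − 0.666)/(0.902 − 0.5) = 0.236/0.402 = 0.59.

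**All scenarios (R² 0.5 to 0.828)**
- Unmatched AUC: 0.73 to 0.94.
- 1- or 2-week ranges: paired AUC about 0.50 to 0.64; 61 to 100% of the AUC above 0.5 is lost.
- Three enrolment groups: paired AUC about 0.54 to 0.73; 43 to 82% lost.
- Within-pair concordance, which respects the matching, shows somewhat smaller losses: 47 to 100% with 1- or 2-week ranges, and 33 to 74% with the three groups.

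**Lower case numbers.** With risk through GA only, 60 to 90% at 28 weeks (about 115 to 147 cases per 787) and R² = 0.828, the unmatched AUCs are 0.868, 0.893 and 0.935. Pairing in the three groups gives 0.590, 0.588 and 0.621, which are drops of 0.278, 0.305 and 0.314. The direction and order of size do not change.

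**The case against.** The strongest reply is that GA pairing suits the aim as written. The hypothesis says respiratory prognosis is useful especially, not only, where GA is unreliable. The aim is association with lung maturity, and the Introduction speaks of prediction in addition to GA. An unmatched contrast would be positive for any proxy of GA and would say little about lung maturity as such. This stands: the paired study should be kept.

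The size also rests on assumptions. If risk runs through GA only, an AUC near 0.50 in narrow ranges is built in, and whether a GA-independent effect exists is exactly what a paired study tests. R² for reflectance alone is unknown, RDS and TTN were pooled under one slope, and the cohort is enriched by the quotas. This stands too, which is why the result is given as a range.

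A reader might infer that pairing is simply a mistake that cancels most of the signal and will make a useful test look useless. The documents do not support that. How much is lost depends on a range width and an independent effect that the article does not give; with broad ranges and a strong independent effect, less than half is lost. Nor does any passage say what would be concluded from a null.

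A reader might also infer that the information is lost. It is not, because reflectance and 72-hour follow-up cover the whole cohort, and the sentence on association tests is not expressly limited to pairs.

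Finally, matching details and supplementary analyses may sit in the full protocol or analysis plan. The point does not rest on their absence. It rests on a control-selection rule that the article states and that cannot by itself answer part of the hypothesis the article states.

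**Conclusion.** The point holds in a limited form. The GA-paired contrast answers a legitimate question, reflectance given GA. It does not answer the part of the main hypothesis on respiratory prognosis without a reliable GA, and it is the only contrast described for the lung outcomes. Pairing removes most of the GA-carried discrimination with 1- or 2-week ranges, and roughly 40 to 80% of the AUC above 0.5 with the three enrolment groups. These figures rest on the assumed risk models, on R² of 0.5 to 0.828, and on the enriched GA mix of the planned cohort. The primary endpoint is unaffected. This is a cheap improvement to a secondary aim, not a fault that invalidates the nested study.

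**What to change.** 1. Keep the GA-paired study, label its question as reflectance given GA, and analyse it with a method that respects the matching.
2. Add a full-cohort analysis of reflectance against RDS and, separately, against TTN, with no matching on or adjustment for GA. Report association, AUC, sensitivity and specificity. Re-weight for the 3:2:1 enrolment quotas to a stated target population, and give results by GA stratum as support. Name this as the answer for settings without a reliable GA.
3. State that a null paired result does not refute prognostic use where GA is unknown.

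The cost is some wording and one extra analysis, with no new infants or measurements. The downside is that the unmatched estimate depends on the GA mix and on the chosen population weights, and partly reflects GA itself rather than lung maturity. The report should say so.
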